**Methods.:**

This mixed-methods study incorporates a prospective cohort study of women with successful vesicovaginal fistula repair at approximately 12 fistula repair centers and affiliated care sites in Uganda (Aims 1–2) followed by qualitative inquiry among key stakeholders (Aim 3). Cohort participants will have a baseline visit at the time of surgery followed by data collection at 2 weeks, 6 weeks, 3 months and quarterly thereafter for 3 years. Primary predictors to be evaluated include patient-related factors, fistula-related factors, fistula repair-related factors, and post-repair behaviors and exposures, collected via structured questionnaire at all data collection points. Clinical exams will be conducted at baseline, 2 weeks post-surgery, and for outcome confirmation at symptom development. Primary outcomes are fistula repair breakdown or fistula recurrence and post-repair incontinence. In-depth interviews will be conducted with cohort participants (n ~ 40) and other key stakeholders (~ 40 including family, peers, community members and clinical/social service providers) to develop feasible and acceptable intervention concepts for adjustment of identified risk factors.

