### Longitudinal cohort study

Our study will recruit a longitudinal cohort of 1,000 women with successful (closed) vesicovaginal fistula repair just after surgery (~ 48 hours later). Participants will be followed for 3 years in total, with data collected via questionnaire at baseline (surgery), 2 weeks (hospital discharge), 6 weeks, 3 months and quarterly thereafter.

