#### Study procedures.

Local study researchers will recruit participants into the cohort following confirmation of successful fistula repair. Potentially eligible women will be identified through review of urogynecology department surgical logbooks, patient medical records, and via direct communication with fistula surgeons and other providers. After fistula repair, women stay at the repair facility for 14 days at a minimum for post-repair catheterization. The local study researcher will approach women at the facility who meet the eligibility criteria in-person 24–48 hrs after surgery to explain the study to them, assess whether they are eligible and, if so, invite them to participate. The study researcher will complete the full informed consent procedure for those women who indicate that they would like to participate, at a convenient time, with the use of a decision tool developed by the University of California San Francisco Human Subjects Research Ethics Board. The study researcher will then collect participant contact information and administer the baseline questionnaire. Participants will be followed through 36 months post-repair, regardless of outcome.

Two-week data collection will occur prior to hospital discharge. Other planned follow-up data collection (6 weeks and quarterly, starting at 3 months) will occur over mobile phone, given high mobile phone penetration across Uganda.^42,43^ Where women do not have their own phone, the study will provide them with a study phone and phone number. Airtime will be provided throughout the study to ensure that study participants have call time (minutes) available and could pay to charge their phone battery as needed.

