#### Measures.

Primary predictors to be investigated include patient-related factors, fistula-related factors, fistula repair-related factors, and post-repair behaviors and exposures (Table 1), collected via structured questionnaire at all follow-up data collection points and from medical records and clinical forms when examinations are performed. Participant sociodemographic, fistula and fistula-repair characteristics will be measured at baseline, with questions on post-repair behaviors and exposures at each follow-up. Outcomes will be screened for at each data collection point; study interviewers will ask a series of questions on signs and symptoms to identify outcomes of interest, women who report new or changed urinary incontinence will be asked to return to the fistula repair facility for clinical exam to confirm fistula breakdown, recurrence, or incontinence. Women with persistent incontinence without fistula breakdown/recurrence will be asked to respond to a short supplemental questionnaire to characterize this incontinence. Women identified as pregnant will be asked to respond to a short supplemental questionnaire on pregnancy-related exposures and outcomes. We seek to develop a comprehensive longitudinal dataset capable of supporting broad inquiry into health and wellbeing following fistula repair.

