Prior to fitting multivariable models, we will calculate the estimated correlation of all potential predictors to identify any highly correlated groups of predictors. We will not include such groups of predictors in any multivariable models. We will assess the adequacy of the proportional hazards assumption through inspection of Schoenfield residuals as a function of time. In the event our data violate the proportional hazards assumption, we will modify our modelling approach to accommodate interactions or stratification, as is most appropriate for the data. We will subsequently fit one multivariable proportional hazards regression model to document the comparative relationship between patient, fistula, fistula repair, and post-repair characteristics and the hazard rate of post-repair fistula breakdown and recurrence integrating all independent variables that were associated with the outcome in bivariable analyses at a conservative p threshold of p < 0.1. Final model selection will be determined via Akaike’s Information Criteria.^52^ Secondary analyses will assess time to post-repair fistula breakdown (< 3 months post-repair) and time to fistula recurrence (≥ 3 months post-repair) separately, and by fistula etiology (obstetric versus iatrogenic), although our study is not powered for secondary outcomes.

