Other methods will also be used to better understand the contribution of risk factors of fistula repair breakdown and recurrence. To overcome the biases inherent to observational research in understanding causal effects,^46^ we propose conducting a series of secondary analyses employing propensity score methods.^47^ Propensity score methods account for systematic differences in baseline characteristics between exposed and unexposed participants, allowing for effects to be interpreted as causal, similar to a randomized experiment.^48,49^ Indeed, propensity score methods may reduce systematic differences between treatment groups compared to covariate adjustment methods.^47^ For these analyses, we will estimate a series of models for each key modifiable factor to be assessed, first developing models predicting the probability of the particular exposure using key baseline and other measures deemed to be relevant for developing the treatment weight, followed by analyses of the exposure and outcome incorporating the treatment weight to the methods described above. Finally, we will seek to construct a classification rule based on predictors using techniques such as recursive partitioning and random forests using routines in R to identify groups of women defined by the exposure characteristics that have high probability of experiencing the adverse outcome.^50^

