**Predictor Variables**							
Patient-related: study participant characteristics, potentially important biological and social risk factors for poor health.							
Sociodemographics	Age, educational attainment	PQ	●				
	Income, assets, food security^58^	PQ	●				●
Obstetric history	Parity, pregnancy outcomes (prefistula, during-fistula), time since fistula development	PQ, MR	●				
Health status	Nutritional status^b^	MR	●	●	●	●	●
	Co-morbidities,^c^ urinary tract infection, functional health,^d^	PQ, MR	●	●	●	●	●
Fistula-related: selected characteristics illustrate fistula severity and physical burden of fistula.							
Fistula characteristics	Size, location, fistula etiology^e^, fistula type^f^, VVF grade^g^, vaginal scarring, bladder capacity, urethral length, bladder neck involvement, other urogyn diagnoses.	MR	●				
Fistula history	Time since fistula development, etiology, symptoms^h^, number of previous repairs, treatments.	PQ, MR	●				
Fistula repair-related: measures include provider training, procedural decisions, and complications.							
Repair procedure	Surgical route^i^; layers, suture type; anesthetic type; sling and tension; flap use, graft use and type, prophylactic antibiotic use, catheterization^j^	MR, PS	●				
Quality of care	Person-centered care	PQ	●				
Provider characteristics	Surgeon, surgical level and experience, repair center	PS	●				
Repair complications	Bleeding, infection, leakage, pain (48hrs+), catheter blockage, other	MR, PS	●				
Post-repair behaviors and exposures: variables capture physical and sexual risks.							
Physical activity and trauma	Moderate and vigorous activity, peak and long-term weight lifting^k^, physical violence^l^	PQ	●	●	●	●	●
Sexual activity and fertility	Post-surgical resumption of sexual activity, frequency of sexual activity, sexual satisfaction^m^, fertility intentions, menstruation, contraceptive use.	PQ	●	●	●	●	●
Lifestyle	Dietary quality, alcohol^n^, tobacco^o^, and caffeine consumption^p^; medical and traditional medical care.	PQ	●	●	●	●	●
Pregnancy-related factors: pregnancy-related factors below may contribute to risk of adverse outcomes through biological or social mechanisms.							
Pregnancy-related health	Chronic and pregnancy-related co-morbidities^q^, timing of pregnancy	PQ, MR	●	●	●	●	●
Antenatal care	ANC initiation, timing, frequency and location, birth planning	PQ, MR	●	●	●	●	●

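### The single multivariable model can adjust surgical technique for repair complications it may cause, hiding the part of its effect that works through them

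*Protocol article*

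**What the plan says.** **Regression.** Under the cohort Data analysis heading of the protocol article, Aim 1 fits one multivariable proportional hazards model across the patient, fistula, fistula repair and post-repair domains, "integrating all independent variables that were associated with the outcome in bivariable analyses" at p < 0.1, with final selection by Akaike's criterion. Highly correlated groups of predictors are kept out. Aim 2 uses the same entry rule for incontinence at 3 months and describes the result as independent and joint effects.

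**Predictors.** Table 1 has a repair procedure row (route, layers, suture, anesthetic, sling, flap, graft, prophylactic antibiotics, catheterization). A separate repair complications row reads "Bleeding, infection, leakage, pain (48hrs+), catheter blockage, other". Both rows are marked only in the baseline column.

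**Timing of baseline.** The abstract says "Cohort participants will have a baseline visit at the time of surgery". Under Study procedures, women are approached "in-person 24–48 hrs after surgery to explain the study to them", and after consent: "The study researcher will then collect participant contact information and administer the baseline questionnaire". Under Measures: "Participant sociodemographic, fistula and fistula-repair characteristics will be measured at baseline".

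**Propensity analyses.** These are secondary. For each key modifiable factor, a model for the exposure is built "using key baseline and other measures deemed to be relevant for developing the treatment weight". The same paragraph says that such methods allow a causal reading.

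**The concern.** A complication that follows the choice of technique and raises the risk of breakdown lies on the path from technique to outcome. Once it is in the model, the technique coefficient no longer measures the total effect. It measures only the part that does not pass through the complication. If complication and outcome share unmeasured causes, conditioning on the complication can add further bias.

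The study wants to find surgical factors, among others, that can become intervention targets. A technique that works mainly by preventing complications could show a coefficient near the null and be dropped by Akaike's criterion, although changing it would help. The complication is likely to pass the p < 0.1 screen because it predicts the outcome. The correlation check takes no account of causal order.

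**Working it through.** The protocol gives no figure on this point, so there is none to reproduce. The check has two parts.

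**1. Can the stated rule put technique and its consequences in one model?**

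- Entry is by bivariable p < 0.1 from all four domains. Technique and complications are both in the fistula repair domain of Table 1.
- The Background describes surgical site infection as an intermediate factor linked to late breakdown. Infection is listed as a complication, and prophylactic antibiotic use as part of the procedure. For that pair, the protocol itself supplies the mediator.
- The only regression estimate certain to be free of complications is the bivariable one. It is also unadjusted for fistula severity, which may influence both technique and outcome.
- The baseline label does not separate before from after for a surgical factor. Number of catheter days is marked at baseline too, although Study procedures gives a minimum of 14 days of post-repair catheterization.

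So joint entry is allowed, and no planned regression is certain to estimate a severity-adjusted technique effect without complications.

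**2. How much could be lost?** All effect sizes below are assumptions.

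*By hand.* Suppose a technique lowers complications from 20% to 10%, complications triple the risk of breakdown, and there is no other effect. The total risk ratio is (0.9 × 1 + 0.1 × 3) / (0.8 × 1 + 0.2 × 3) = 1.2 / 1.4 = 0.86. Within women with a complication, and within women without, it is 1.00.

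*By simulation, 1,000,000 women per scenario.*

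- Pre-operative severity S is standard normal.
- Technique X has logit 0.6 S.
- Complication M has logit −1.7 + ln(OR) X + 0.4 S.
- Outcome risk is 1 − exp(−0.12 × HR_direct^X × HR_M^M × exp(0.3 S)). This gives 13.5% to 15.1% in women without the technique, near the 15% in the Sample size section.

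Regression is complementary log-log, and weighting is inverse-probability. Entries are hazard ratios (regression) or cumulative-hazard ratios (true value, weighting) for X.

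| Scenario (direct HR; OR of X on M; HR of M on outcome) | True total | Regression: S, then S + M | Weighting: S, then S + M |
|---|---|---|---|
| Full mediation (1.0; 2.5; 3.0) | 1.23 | 1.24, then 1.01 | 1.24, then 1.00 |
| Partial (1.2; 2.5; 3.0) | 1.47 | 1.48, then 1.21 | 1.47, then 1.19 |
| Weak (1.5; 1.5; 2.0) | 1.56 | 1.56, then 1.49 | 1.55, then 1.47 |
| None (1.5; 1.0; 3.0) | 1.47 | 1.49, then 1.51 | 1.48, then 1.48 |

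Share of the regression excess over 1 that is lost:

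- full: (0.24 − 0.01) / 0.24 = 96%
- partial: (0.48 − 0.21) / 0.48 = 56%
- weak: (0.56 − 0.49) / 0.56 = 13%
- none: no loss

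Adjusting for pre-operative severity alone recovers the true total effect in every scenario. The harm comes from adding the complication. The simulation has no unmeasured cause shared by complication and outcome, so it does not show the additional bias that such a cause could bring.

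**The case against.** The strongest reply is that the aim is to identify predictors. Mutual adjustment across domains is ordinary for that purpose, and an independent effect is by definition conditional on the other predictors. Joint entry is possible under the rule but not certain, and the bivariable results would still be reported. This stands as far as prediction goes. It does not supply a severity-adjusted total effect of technique, which a search for modifiable surgical targets needs.

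The illustrations rest on invented inputs. The hand example is the extreme of full mediation, and its 0.86 is 1 / 0.857 = 1.17 in the other direction, below the hazard ratio of 1.2 for which the protocol claims power. That is fair, and it is why the result is given as a range from nearly all to none.

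A reader might infer more than the protocol supports, in three ways.

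- **That balancing on baseline measures is itself wrong because the visit is post-operative.** It is not. Age, parity, fistula size, location, etiology and previous repairs describe the state before surgery, whenever they are written down. They must be balanced.
- **That the propensity analyses are planned with this fault.** The text names neither technique as an exposure nor complications as weight covariates, and detailed covariate lists may sit in a document not shown. What remains is loose wording beside a claim of causal interpretation.
- **That person-centered care and all baseline health measures are consequences of technique.** Nothing in the protocol shows this, and several listed co-morbidities are chronic.

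Table 1 also does not say whether bleeding is intra- or post-operative, so its order relative to some technical choices is unknown.

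**Conclusion.** The point holds for the multivariable models of both aims. As written, the entry rule allows technique to be adjusted for complications it may cause, and it provides no severity-adjusted estimate that is certain to avoid this. The loss is the mediated part of the effect: from nearly all to none in the illustration, depending on assumed effect sizes that the protocol does not give. Under full mediation a hazard ratio of 1.24, just above the 1.2 at which the protocol claims power, became 1.01.

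For the propensity analyses it is a conditional caution that applies only if a surgical factor is chosen as an exposure. Post-repair exposures such as activity, sexual activity and pregnancy are generally unaffected, because the post-operative baseline usually precedes them. This is a worthwhile, inexpensive improvement. It does not invalidate the cohort or its predictive analyses.

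**What to change.** 1. For each outcome, estimate technique effects from a model adjusted for pre-operative patient and fistula characteristics and for surgeon/center. Leave out post-operative complications and later post-repair variables, whatever their bivariable p value.
2. Add complications in a second model. Label it as a direct-effect or predictive model, and do not read its technique coefficients as total effects.
3. If a surgical factor is used as a propensity exposure, build its weight only from variables fixed before the operation. Pre-operative facts merely recorded at the post-operative baseline visit stay in, and post-operative complications stay out.
4. State whether bleeding and similar items are intra- or post-operative, so that each can be placed before or after the technique in question.

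The cost is a few sentences of analysis text and one extra model per outcome. The models need no new data collection.

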#### Sample size.

The sample size for our longitudinal cohort study (up to n = 1000 women) was calculated to provide adequate power to detect a minimum difference in effect for patient-related, fistula-related, fistula-repair related, post-repair behaviors and exposures on risk of fistula repair breakdown or recurrence and incontinence of 20% (Aims 1 and 2) using the log-rank test for two-sample comparison of survivor functions (Aim 1) and the Pearson’s chi-squared two-sample proportions test (Aim 2). These effect differences were determined to be clinically significant based on expert opinion.

Power calculations were developed using Stata’s power procedure, with values α = 0.05 and 1-β = 0.80.^51^ Prior research on fistula recurrence risk elsewhere suggests that factors of interest for our survival analyses (Aim 1) may have hazard ratios ranging from 1.0 to 3.4.^14^
Fig. 4 below illustrates the minimum sample size required for estimation of effect estimates ranging from 1.1 to 2.0 with parameters α = 0.05 and 1-β = 0.80, illustrating adequate power for two-sample comparison of survivor functions (i.e., time to fistula repair breakdown, time to fistula recurrence) with a sample size of 1000 for effect estimates (hazard ratios) of 1.2 or higher, illustrating a 20% or higher risk difference, accommodating some loss to follow-up. Research in other locations has reported a repair breakdown or recurrence rate of approximately 15%. With our target sample size of 1000, we anticipate being able to estimate this incidence with a range of precision of approximately 2.5% (i.e., between 12.8%−17.4%).

Sample size calculations for comparisons between risk factors of post-repair urinary incontinence at 6 and 12 months informing this analysis were estimated using the Pearson’s chi-squared two-sample proportions test with parameters α = 0.05 and 1-β = 0.80. The prior literature does not provide a good estimate of what range of potential risk elevation we are likely to see, so we have estimated risk differences of approximately 10 percentage points, across a range of possibilities. As shown in Fig. 4, for a potential comparison of 9 percentage points (e.g., from 1–10%) we achieve power of 0.80 at approximately 200 study participants. On the other end of the range (e.g., a comparison between 50% and 60%; Fig. 6), statistical power of 0.80 is achieved with a minimum sample size of 800 participants.

### Qualitative Component

Qualitative research with key stakeholders will be conducted to inform the development of feasible and acceptable intervention concepts targeting risk factors identified from our longitudinal cohort aims (Aims 1–2).

#### Study participants.

We will enroll approximately 80 individuals in total, including women with fistula, family members, community members, clinical and social service providers, and government. We will purposively sample ~ 40 longitudinal cohort participants to reflect study variability in region and adverse outcome experience. Other key stakeholders (~ 40) will be identified through discussion with study investigators, site leads and research assistants, and other clinical and social service providers for fistula in Uganda, to maximize variability in respondent region and clinical and patient support roles. Identified individuals will be invited to participate over the phone, email, or in-person and those who are interested and are willing to provide informed consent will be scheduled for an in-depth interview with a trained qualitative interviewer at a convenient time and private location. Informed consent for all respondents will be conducted in person, with written or thumbprint confirmation obtained, as appropriate. To respect the privacy and confidentiality of longitudinal cohort participants, permission will first be sought from the research participant before recruiting potential family member or peer qualitative participants.

#### Study procedures.

Based on our quantitative findings (Aims 1 and 2), literature, and expert clinical and contextual experience, the research team will develop a semi-structured and open-ended in-depth interview guide for key stakeholder interviews to obtain a nuanced understanding of their perspectives on feasible and acceptable potential intervention opportunities for addressing key risk and causal factors associated with adverse outcomes. Exploration of intervention possibilities with stakeholders may employ constructs from health behavior theories COM-B (‘capability’, ‘opportunity’, ‘motivation’, and ‘behavior’) model (Fig. 5) and the theoretical domains framework (TDF) for understanding individual and contextual issues, and the Consolidated Framework for Implementation Research (CFIR) for pre-implementation assessment of factors important to successful implementation (i.e., intervention characteristics, inner setting (characteristics of implementing organization), outer setting (features of the external context or environment), and implementation process (strategies or tactics for implementation setup or delivery).^52,53^ Interviews will be conducted in a private setting by an experienced qualitative interviewer and are anticipated to take 1–2 hours. Participants may be asked to respond iteratively as new data arises during the qualitative process. Interviews will be audio recorded and translated into English and transcribed.

